**Resident level data**	
Age and gender	Baseline
Date of admission and discharge and reason for discharge from the facility	Baseline and monthly
Diagnosis	Baseline and at 12 months
Number and list of regular and PRN medications including dosages	Baseline and at 12 months
Emergency Department visit/transfer*	Baseline and monthly
Hospital admissions* and length of hospital stay as determined by RACF residents’ records	Baseline and monthly
Reason for Emergency Department visit/admission to hospital - as determined by RACF residents’ records	Baseline and monthly

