## Background

Older adults residing in residential aged care facilities (RACFs) generally have complex co-morbidities and are prescribed a large number of different medications [1]. Studies have reported that, on average, RACF residents take between 9 and 11 regular medications [2–4]. Polypharmacy increases the risk of medication-related problems and adverse drug events, including hospitalisations, placing a significant burden on residents and economic cost on the health care system [5–7]. Australian studies have shown that almost all RACF residents have at least one medication-related problem [4, 8–11] and between 30% and 73% of residents are prescribed at least one potentially inappropriate medication (PIM) [4, 12–18]. According to a recent meta-analysis of 33 international studies, the use of PIM is significantly associated with an increased risk of hospitalisation in the older population, and the risk was higher in those who took more than one PIM [19]. Additionally, PIMs are associated with other potential adverse outcomes in older indivisuals, including fall, fracture, cognitive decline, delirium, stroke and cardiovascular events [20, 21].

Among PIMs, sedatives, antipsychotics and drugs with anticholinergic properties are particularly associated with greater risk of harm. A large Australian cohort study among 11,368 residents found that 61% were taking psychotropic medications, with the majority of these agents having sedative properties that can contribute to falls or confusion [22]. The over-use of psychotropic medications has been recently highlighted in the interim report of the Australian Royal Commission into Aged Care Quality and Safety [23]. Australian studies have reported that over 20% of RACF residents were taking antipsychotics regularly [22, 24], and the duration of antipsychotic use was longer than recommended [25–27]. Prolonged use of antipsychotics in older people is linked with increased risk of hospitalisation, hip fracture, peneumonia, stroke and death [28, 29]. Another large Australian study [30] of 17,000 RACF residents reported that 46% were taking drugs with moderate to strong anticholinergic effects; these drugs can contribute to cognitive and functional decline, delirium, worsening dementia, and increased mortality in older people [31].

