#### Primary outcome

Change in proportion of residents who are prescribed at least one PIM (from baseline to 12 months) according to the 2019 Beers Criteria [52]

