**Facility level data**	
Number of permanent residents, proportion of residents with dementia, and proportion receiving the highest level of government funding	Baseline and at 12 months
Number of RACF registered nurses rostered during day/night/weekend	Baseline and at 12 months
Care staff turn-over reported by RACFs	Baseline
Total number of beds and bed occupancy rate	Baseline
Resident turn over	Monthly
Number of medication-related incidents	Monthly
Number of resident falls	Monthly
Time taken to conduct medication rounds	Baseline and at 12 months
% of staff/residents received influenza vaccination	At one time point
% of residents that have drug allergy and adverse drug reactions documented	Baseline and at 12 months
Number of GPs visiting residents in facility	Baseline
RACF managers perceived top 5 reasons for unplanned hospitalisations of residents in previous 12 months, and possible solutions for reducing these	Baseline

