### Statistical analysis

Descriptive statistics will be used to summarise and compare the data at the RACF level in each group at baseline and at the end of the trial, including primary and secondary outcomes as well as additional potential confounder variables (such as demographic profile, duration of residency, presence of dementia, Charlson comorbidity index [59] and number of medical conditions).

Bivariate analyses for group comparisons will use either t tests or ANOVA for data that are normally distributed, Mann-Whitney U and Kruskall-Wallis tests for data that are not normally distributed, or chi-square-based analysis for categorical outcome data. For within group comparisons, paired t tests and repeated measures ANOVAs will be used; if variables are not normally distributed, the Wilcoxon signed-ranks and Freedman tests will be used, while the McNemar test will be used for changes in proportions.

To determine the effect of the intervention on the outcome measures and the changes over time (between-within group effects), multilevel modelling methods, which take into consideration the hierarchical structure of the data (including clustering within RACF and repeated measurement occasions) will be applied. These modelling methods will include mixed-effects generalised linear models (Logistic and Poisson regression models) for binary and count outcomes as well as mixed-effects linear models for continuous outcomes assumed to have a normal distribution, or otherwise transformed to meet the assumption.

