Analysis will be weighted by cluster size as required. Interactions and adjusting for demographic characteristics and other potential covariates will be included when deemed necessary. Residents who enter, die or move from RACFs after baseline data collection will have only one data point and will be included in the analysis. When data are missing at random, patterns of missing data will be evaluated, and potential predictors of missing responses will be investigated. Methodological attempts to fill in missing data will be extensively explored and applied as appropriate. These include single imputation approaches (such as regression imputation and nearest neighbours or hot-deck imputation) and multiple imputation approaches. Analysis will be conducted using either SPSS version 26 or STATA version 16. Significance level will be set at the usual 5% alpha-level (two-tailed where applicable). All estimated effects will be reported along with their 95% confidence intervals.

Since the sample size and power calculation have been devised based on the primary outcome and hypothesis, the level of adjustment and number of potential covariates to adjust for may be limited by the sample size and the response rate. Posterior power calculations will be performed based on available sample size and the secondary outcomes.

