### Safety evaluation and reporting

RACFs are required to have clinical governance processes and complaints procedures in place. Criteria for monitoring the trial are informed by Stallard [61], whereby adverse events will be monitored and the trial ceased if there is evidence of harm. All adverse events will be entered into an *Adverse Event Log* and reported to external clinical consultants to determine whether or not they are considered causally related to study. For every adverse event, researchers and external consultants will provide an assessment of the severity, causal relationship to the study, outcomes and seriousness of the event, and document all actions and inform the Human Research Ethics Committee. In light of the COVID-19 pandemic, the research team will follow all RACF’s safety protocols and guidelines when they visit RACFs to ensure the safety of the residents and RACF staff.

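### All-cause mortality is neither an outcome nor a planned comparison between arms, and admission, ED and fall rates are stated per resident with no time at risk

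*Protocol article*

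**What the plan says.** **Outcomes.** The primary outcome is the change in the proportion of residents with at least one potentially inappropriate medicine. The secondary list covers ED presentations and admissions, falls, psychotropic use and dose, anticholinergic burden, medication incidents, staff vaccination, medication-round time and costs. Death is in neither list. ED presentations with admissions, and falls, are each given as a rate per resident over 12 months.

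**Data.** Table 2, resident level, collects "Date of admission and discharge and reason for discharge from the facility" at baseline and monthly.

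**Analysis.** Count outcomes fall under "mixed-effects generalised linear models (Logistic and Poisson regression models) for binary and count outcomes". No exposure offset is stated or excluded. Death appears once in the statistical section: "Residents who enter, die or move from RACFs after baseline data collection will have only one data point and will be included in the analysis".

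**Safety.** Under Safety evaluation and reporting, "adverse events will be monitored and the trial ceased if there is evidence of harm". Each event is assessed with external consultants for severity, seriousness and causality, and the researchers and consultants "document all actions and inform the Human Research Ethics Committee".

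**Rationale.** The Background states: "Prolonged use of antipsychotics in older people is linked with increased risk of hospitalisation, hip fracture, peneumonia, stroke and death". It also names increased mortality among the harms of anticholinergic medicines.

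**The concern.** The Background links the targeted medicines to falls, hospitalisation and death. Falls and hospitalisation became outcomes and death did not, although the plan expects deaths and collects what is needed to count them. An outcome list belongs to the protocol, so this gap is not one that an analysis plan would ordinarily fill.

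Two things are at stake. First, the results meant for policymakers would contain no planned estimate of the effect on survival, in either direction. Second, a resident who dies in month 3 can have no admission, ED visit or fall in months 4 to 12. With a denominator of residents and not resident-time, the arm with more deaths looks better on these outcomes. A reader who sees a small reduction in admissions could not tell from the planned results how much of it came from shorter time at risk.

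**Working it through.** **Where death could enter the results**

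| Section | What it does with death |
|---|---|
| Primary and secondary outcomes | Not listed |
| Table 2 | Exit date and reason, monthly; death not named, but the statistical section lists dying as a way of leaving |
| Statistical analysis | Residents who die are kept with one data point; no comparison of deaths |
| Economic evaluation | No comparison of deaths |
| Safety evaluation | Adverse events reviewed one by one; death not named, arms not compared |

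**The plan's own figures, for the denominators.** Design effect 1 + (93 − 1) × 0.05 = 5.6. Then 5.6 × 106 = 593.6, or 594 per arm and 1188 in total. 1188 / 93 = 12.8, so 13 sites. This agrees with the Sample size section.

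**Size of the artefact in admissions.** The documents give no mortality figure, so 20% to 40% over 12 months is an assumption. Further assumptions are a constant death hazard, residents present from baseline with death as the only exit, the same admission rate while alive in both arms, and a denominator that counts residents. With 12-month mortality m, mean follow-up in years is

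f(m) = m / (−ln(1 − m)),

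which gives f(0.20) = 0.896, f(0.25) = 0.869, f(0.30) = 0.841, f(0.35) = 0.812 and f(0.40) = 0.783. The apparent rate ratio per resident is f(intervention) / f(control).

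| Control mortality | Intervention mortality | Excess | Ratio per resident | Ratio per resident-time |
|---|---|---|---|---|
| 20% | 25% | 5 points | 0.97 | 1.00 |
| 30% | 35% | 5 points | 0.97 | 1.00 |
| 20% | 30% | 10 points | 0.94 | 1.00 |
| 25% | 35% | 10 points | 0.94 | 1.00 |
| 30% | 40% | 10 points | 0.93 | 1.00 |

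The spurious reduction is therefore about 3% for a 5-point excess and 6% to 7% for a 10-point excess. It disappears when resident-time is the denominator.

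**Number of deaths.** 1188 × 0.20 = 238 and 1188 × 0.40 = 475 across both arms. A 5-point excess is 594 × 0.05 = 30 deaths in one arm.

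**Precision of a mortality estimate.** Take 25% mortality (assumed), 594 per arm and design effect D. The 95% half-width for the difference is 1.96 × √(2 × 0.25 × 0.75 × D / 594).

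- ICC 0.05 (the plan's value, set for the prescribing outcome): D = 5.6, √0.00354 = 0.0595, half-width ±11.7 points.
- ICC 0.01 (assumed): D = 1 + 92 × 0.01 = 1.92, √0.00121 = 0.0348, half-width ±6.8 points.

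These are normal approximations; with about 13 facilities a small-sample interval would be somewhat wider. Power for 30% against 35% is about 26% at ICC 0.01 and 12% at ICC 0.05.

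**The case against.** The strongest reply has four parts.

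- **The safety section exists.** A reader might infer that deaths would go unreported. The document does not support that: all adverse events are logged, reviewed by external consultants and notified to the ethics committee, and the trial stops on evidence of harm. This reply stands against that inference. It does not supply a comparison. In a frail population an excess of deaths is hard to recognise case by case and shows mainly as a difference between arms, which this route does not set out.
- **A time-at-risk offset may be planned.** The Poisson models permit one, the dates are collected, and such detail often sits in a full protocol or analysis plan, neither of which is shown. This also stands in part. An offset would remove the artefact, but it would not report survival. The article as written fixes the rate per resident.
- **The artefact is small and the mortality estimate imprecise.** Both are true, as the figures show. They limit the importance of the point without removing it.
- **Prescribing prevalence is a separate matter.** A reader might also infer that mortality would distort the primary outcome. That is not shown. It would require deaths to be related to inappropriate prescribing, and differently so by arm. The documents give no evidence of this, and the plan keeps residents who die in the multilevel model with the data they have.

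**Conclusion.** The point holds in a limited form. The protocol fixes an outcome list without all-cause mortality and plans no comparison of deaths between arms, although its own rationale cites death as a harm and the exit records are collected monthly. Stating admissions, ED visits and falls per resident lets an excess of deaths pass for a benefit. The effect is modest: about 3% to 7% for an excess of 5 to 10 points.

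That size rests on the assumed mortality of 20% to 40%, a constant hazard, and a denominator that counts residents. That deaths can be read from the reason for discharge is an inference, though a natural one. The primary analysis is not threatened. This is an inexpensive improvement to what the safety and admission results can support.

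**What to change.** 1. Add all-cause mortality over 12 months as a secondary safety outcome. Count deaths and resident-time by arm from the monthly discharge records, and estimate a rate ratio or hazard ratio that allows for clustering by facility, with its 95% CI. Report it directly beside the ED and admission results.
2. Express ED visits, admissions and falls per resident-time at risk, with log time as the offset in the Poisson models. Table 2 collects falls as a monthly facility count, so there the offset is the facility's total resident-time.
3. State that death is a coded category of the reason for discharge, so that the count does not depend on inference.

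**Cost.** One further outcome and a changed denominator, with no new data items. The drawback is a wide interval for mortality, roughly ±7 to ±12 percentage points for an ICC of 0.01 to 0.05. It should be presented as an estimate, and an interval that includes no difference should not be read as showing that survival is unaffected.

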**Intervention pharmacist activity data**	
Daily activities and time taken to conduct each activity	Daily

*Outpatient appointments & scheduled procedures will not be included in hospital admission/emergency department visit data

### Sample size

It was estimated that a conventional RCT with randomisation of individuals would be able to detect a reduction from 60 to 40% of residents having at least one PIM [14], with a minimum of 106 residents in each arm (total of 212 residents in both arms) with a significance level of 5%, a power of 80% on equal allocation and a response rate of 85%. By adjusting for the loss of power due to clustering, with an intra-cluster correlation coefficient of 0.05 and a cluster size of 93 residents per RACF, the estimated sample size is (1 + [(93–1) x 0.05] =5.6 x 106) or 594 residents in each arm (1188 in both arms), equating to a minimum of 13 sites. The sample size was calculated using G*Power 3.1.9.4 [57].

The estimated prevalence of PIM in RACFs at baseline (60%) was based on previous studies in which the prevalence of PIM in Australian RACF residents were reported as 73% in 2018 [16], 49% in 2014 [14] and 56% in 2012 [58].

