**Methods:**

Intervention aged care facilities will employ on-site pharmacists to work as part of their healthcare teams 2 to 2.5 days per week for 12 months. On-site pharmacists, in collaboration with facility nurses, prescribers, community pharmacists, residents and families will conduct medication management activities to improve the quality use of medicines. Aged care facilities in the control group will continue usual care. The target sample size is 1188 residents from a minimum of 13 aged care facilities. The primary outcome is the appropriateness of prescribing, measured by the proportion of residents who are prescribed at least one potentially inappropriate medicine according to the 2019 Beers Criteria. Secondary outcomes include hospital and emergency department presentations, fall rates, prevalence and dose of antipsychotics and benzodiazepines, Anticholinergic Cognitive Burden Score, staff influenza vaccination rate, time spent on medication rounds, appropriateness of dose form modification and completeness of resident’s allergy and adverse drug reaction documentation. A cost-consequence and cost-effectiveness analysis will be embedded in the trial.

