### Participants

#### RACFs

All RACFs in the ACT that are nationally accredited facilities will be invited to participate in the trial. RACFs that have less than 20 beds will be excluded. There are a total number of 1978 RACF beds in facilities in the ACT, and the ACT had a population of 431,000 in 2020 [53].

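### The sample size names an 85% response rate that 106, 594 and 1188 do not contain, and equal arms of 594 from facilities of 93 need 14 sites, not 13

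*Protocol article*

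**What the plan says.** The Sample size section starts from an individually randomised trial able to "detect a reduction from 60 to 40% of residents having at least one PIM", "with a minimum of 106 residents in each arm (total of 212 residents in both arms"). The stated inputs are completed "with a significance level of 5%, a power of 80% on equal allocation and a response rate of 85" per cent. Clustering is then added "with an intra-cluster correlation coefficient of 0.05 and a cluster size of 93 residents per RACF", giving a design effect of 5.6, "or 594 residents in each arm (1188 in both arms), equating to a minimum of 13 sites". The abstract repeats the result: "The target sample size is 1188 residents from a minimum of 13 aged care facilities".

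Sidedness is given only under Statistical analysis: "Significance level will be set at the usual 5% alpha-level (two-tailed where applicable"). Randomisation is by facility and stratified by facility size. On the range of sizes, the RACFs section says only "RACFs that have less than 20 beds will be excluded".

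**The concern.** The response rate is listed beside significance level, power and allocation as an input to 106, so a reader takes 106, and therefore 594 and 1188, to allow already for 15% loss. No step applies it, and 106 looks like the answer without it.

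The site count also comes from dividing the total by 93, not each arm, although whole facilities are randomised and equal allocation is assumed.

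The stated 80% power is one basis on which a null primary result would be read. If the allowance is absent, the margin against non-response that the text implies does not exist.

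**Working it through.** **Inputs.** From the Sample size section: 60% v 40%, 5%, 80% power, equal allocation, 85% response, ICC 0.05, 93 residents per facility. From Statistical analysis: two-tailed testing.

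**1. Reproducing 106, no loss**
- Pooled z: n = [1.960 × √(2 × 0.5 × 0.5) + 0.842 × √(0.24 + 0.24)]² / 0.2² = (1.386 + 0.583)² / 0.04 = 96.9, so 97.
- Continuity-corrected: (96.9/4) × [1 + √(1 + 4/(96.9 × 0.2))]² = 106.7, so 107.
- Exact Fisher: power 78.9% at 106 and 80.2% at 108. Exact power moves in steps: it touches 80.1% at 102, drops to 77.5% at 103 and passes 80% again at 108.

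So 106 matches the corrected or near-exact figure before any loss.

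**2. Applying the 85%**
- 97/0.85 = 114.1, so 115.
- 107/0.85 = 125.9, so 126.
- 108/0.85 = 127.1, so 128.
- One-sided at 80% power, after dividing by 0.85: 91 (pooled), 102 (corrected), 100 (exact).

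None of these gives 106. A one-sided pooled calculation at 90% power also gives 106, but that is not the stated power and again contains no loss.

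**3. Clustering as stated**
- Design effect: 1 + 92 × 0.05 = 5.6.
- 5.6 × 106 = 593.6, so 594 per arm and 1188 in total.
- 1188/93 = 12.8, so 13 sites.

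These figures reproduce, and they inherit the missing allowance.

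**4. Power at 1188 if 85% are analysed** (594 × 0.85 = 504.9 per arm)

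If the analysed cluster shrinks to 93 × 0.85 = 79.05, the design effect is 1 + 78.05 × 0.05 = 4.90.

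| Case | Effective n per arm | z | Corrected | Exact |
|---|---|---|---|---|
| No loss, design effect 5.6 | 106 | 83% | 80% | 79% |
| 85%, design effect held at 5.6 | 504.9/5.6 = 90 | 77% | 72% | 71% |
| 85%, design effect 4.90 | 504.9/4.90 = 103 | 82% | 78% | 77% |

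(The exact figure in the last cell is 77.5%.)

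**5. Enrolment per arm if the 85% is applied** (115, 126, 128 times the design effect)
- At 5.6: 644, 706, 717.
- At 4.90: 564, 618, 628.

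The planned 594 exceeds the z-test requirement in the second row and is 4-6% below the other two (618/594 = 1.04; 628/594 = 1.06).

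**6. Sites**
- 594/93 = 6.39, so equal arms of at least 594 need 7 + 7 = 14 facilities.
- Thirteen split 6 v 7 give 558 v 651 (1209 in total). Power by z test is 83.9%, against 83.5% for 594 v 594; corrected, 80.3% against 79.7%.

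**7. Few facilities.** This is a 12-month-only comparison at facility level with equal sizes and a non-central t distribution. The standard error is √[design effect × 0.24 × (1/n₁ + 1/n₂)].
- 6 v 7, no loss: √[5.6 × 0.24 × (1/558 + 1/651)] = 0.0669. The non-centrality is 0.2/0.0669 = 2.99, with 11 degrees of freedom and critical value 2.20. Power is 77.7%.
- 6 v 7, 85% analysed, design effect 4.90: 76.5%.
- 7 v 7: 81.5% with no loss, 80.4% with 85% analysed.

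**The case against.** **The effect of the 85% is not fixed by the text.** Residents are included unless they opt out, data come from facility records, and residents with a single data point stay in the analysis. The article does not say whether 93 counts enrolled or analysed residents. If loss also shrinks the analysed cluster, the design effect falls and most of the loss is recovered: power is 82% by z test and 78% on the corrected test that reproduces 106. This stands. It rules out a flat statement that the trial lacks 80% power. It does not explain how 106 could contain the 85%.

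**Thirteen is a minimum, and facilities differ in size.** This stands too. A reader might infer that the odd site count causes a power loss; step 6 shows that it does not. What remains is that 13 facilities of 93 cannot supply two arms of 594.

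**The 11-degree-of-freedom figure ignores baseline data.** The plan is a multilevel model with repeated measurements. If baseline and 12-month facility means correlated at 0.4 (an assumption), the same t calculation with 10 degrees of freedom gives about 84% at full response and 83% at 85%; at 0.3 it gives about 81% and 79%. Small-sample methods are also commonly left to an analysis plan. So the 77-78% describes one simple analysis, not the trial's power.

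**Unequal facility sizes.** A reader might go further and put power at about 69-76%. That needs a coefficient of variation of facility size of 0.4-0.5, which the documents do not give; they offer only the 20-bed floor, stratification by size and optional weighting by cluster size.

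**Conclusion.** The point holds as an error of statement. The four listed inputs and 106 cannot all be true: 106 is the no-loss figure, and 594 and 1188 carry no allowance for non-response. The conclusion assumes the two-sided 5% level and the stated 80% power.

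The consequence for power is a range. With 85% analysed it is 71-77% if the design effect stays at 5.6 and 77-82% if it falls to 4.90, depending on the test. A reader might infer that 1188 residents at 13 sites cannot reach 80% even if the ICC and the 20-point effect are right. The documents do not support that, because one plausible reading gives 82% and the planned use of baseline data could add power.

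The site count is a smaller inconsistency: 14 facilities, not 13, for equal arms of 594. In a 12-month-only facility-level comparison with equal sizes, 13 sites give about 78% (77% with 85% response) and 14 give about 80-81%.

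**What to change.** In the Sample size section and the abstract, do one of the following:

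- State that 106, 594 and 1188 carry no allowance for non-response, and restate the power with 85% analysed, naming the test and the design effect used.
- Show the inflation step, and say whether 93 is the enrolled or the analysed number per facility so that the design effect matches. Step 5 gives the resulting targets. The choice of convention moves them from 564-628 to 644-717 per arm, so neither set should be quoted without it.

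In either case, state that 13 sites covers the total of 1188 only, and that equal arms of 594 from facilities of 93 need 14. Once the recruited facilities are known, it would help to give the power at their actual number and sizes.

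The cost is rewording and a slightly less favourable stated power. No extra enrolment is required to correct the statement.
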